## Abstract

Background: Sleep disturbances are common among athletes. There is recently a growing interest in improving sleep quality by using noninvasive brain stimulation techniques such as transcranial direct current stimulation (tDCS). We hypothesized that bilateral dorsolateral prefrontal cortex anodal tDCS could improve sleep in different sports athletes. A randomized controlled trial is to be conducted to test this hypothesis. Methods: Eighty-four athletes are selected based on specific eligibility criteria and randomly allocated to the intervention or control group. Each participant will receive a 20-min session of bilateral anodal tDCS with an intensity of 1.5 mA (0.057 mA/cm^2^) in density 3 times a week for 2 weeks. The tDCS current will be delivered only for 30 seconds in the control group. This study’s outcome is a set of subjective and objective sleep parameters. Conclusion: This study assessed the effect of a novel tDCS protocol represented by bilateral anodal stimulation and may result in important advances in sleep management among athletes. Because of the high incidence and impact of athletes’ poor sleep quality, it is particularly important to explore effective interventions. Trial Registration: ClinicalTrials.gov: NCT05318352.

## 1. Introduction

Sleep disturbances are common among athletes [1]. The prevalence of high sleep disturbances is between 50 and 78% among elite athletes [2], which is more prevalent compared with non-athletic populations [3]. The sleep disturbances among athletes are generally characterized by poor sleep quality, daytime sleepiness, and habitual short sleep [2,4,5]. Different studies showed that disturbed sleep negatively affects overall athlete performance, anxiety, and physical and mental fatigue [6]. Sleep disorders are multifactorial, including sport and non-sport factors. The sport factors may include high training loads, unfamiliar sleeping environments, early morning training, long-haul travel, and night competitions [7,8,9,10]. On the other hand, individual chromatics, social demands, and habits may be considered non-sport factors [11].

A set of neuroimaging studies have identified a broad range of structural and functional changes in different brain areas in people with sleep disorders [12,13,14]. For example, people with insomnia and other sleep disorders exhibited decreasing metabolism in cortical-subcortical structures such as the bilateral prefrontal cortices, reticular activating system, and the left superior temporal, parietal, and occipital cortices [12,13,14]. Furthermore, the reduction in prefrontal cortex activity is directly linked to attentional reduction and cognitive flexibility impairments resulting from sleep insufficiency [15]. In this context, there is growing interest in the management of sleep disorders by utilizing invasive and noninvasive brain stimulation. Transcranial direct current stimulation (tDCS) is noninvasive brain stimulation that has been used in clinical trials to improve sleep in healthy and clinical populations [16].

tDCS may improve sleep indices through modulation of cortical activity and slowing oscillatory activity (<1 Hz) [17]. Slowing oscillatory activity is essential for the generation of oscillatory cycles that systematize brain activity during sleep [18]. It is considered the neurophysiological marker of slow wave activity (0.5–4.5 Hz) during the non-rapid eye movement (NREM) sleep stage [19]. The anodal stimulation for frontal areas can slow oscillation in the stimulated area and increase the activity of cortical and subcortical structures [17]. Therefore, we hypothesized that anodal stimulation of bilateral prefrontal cortices could improve sleep in athletes with poor sleep quality.

The current evidence shows some interventions inducing sleep in athletes [20]. Sleep education, sleep hygiene, nutritional plans, and encouraging short sleep nap opportunities are commonly used interventions in athletic populations [21,22]. However, adherence to those interventions in athletes is challenging. Furthermore, examining sleep in sports research has several limitations, such as inadequate experimental control, lack of females, and relying on self-reported sleep outcomes [1]. Therefore, there is a need for high-quality randomized controlled trials (RCTs) that assess the efficacy of alternative robust methods such as tDCS in different sports athletes. To our knowledge, there is only one clinical trial that examined the effect of tDCS on sleep in athletes and found improvement in some sleep parameters [23]. It included a small sample of athletes. We think that the effect of tDCS on sleep disorders in athletes is still unclear. Further robust studies are required to conclude the effect of tDCS on sleep for athletes. Hence, this RCT will aim to assess the effect of bilateral anodal tDCS over the right and left dorsolateral prefrontal cortices (DLPFCs) on a set of subjective and objective sleep parameters among athletes with poor sleep quality using a statistically powerful sample size.

## 2. Materials and Methods

### 2.1. Participants

Participant recruitment began in May 2022 and will continue until December 2023. Athletes from the national clubs and teams of different sports in Jordan will be invited to participate in this study. Elite athletes are eligible if they satisfy the following criteria: (1) being 16 years of age and older and (2) have a complaint of sleep impairment determined by a global score >5 on the Pittsburgh Sleep Quality Index (PSQI).

Exclusion criteria for the study will include any of the following: the use of sleep medications or other interventions interfering with sleep and sleepiness, more than one concussion in the past year, using a pacemaker, pregnancy, diagnosis of migraines with a high frequency of episodes, wearing a metal implant, or epilepsy. 

### 2.2. Study Design

The study design is a prospective, double-blinded RCT. It will be reported according to the Consolidated Standards of Reporting Trials (CONSORT) statement for non-pharmacological treatment [24]. The study was approved by the institutional review board council at the University of Jordan (80-2021, 11 August 2021). The clinical trial is registered with the clinicaltrials.gov web site (registration number: NCT05318352). All participants will sign written informed consent prior to participation according to the Declaration of Helsinki.

### 2.3. Randomization Allocation and Blinding

Participants will be allocated consecutively to randomization using the tool from the randomization.com website (http://www.randomization.com, Accessed date: 10 May 2022) by a researcher who is not in contact with any participant. The investigators will use the suggested first generation for RCT studies. The included participants will be randomly allocated to the parallel tDCS or control groups in a balanced allocation ratio of 1:1. Allocation concealment will continue until the end of the study.

All assessment, evaluation, and intervention procedures will be carried out by examiners who will be blinded to the allocation of the participants. A trained research assistant that is not otherwise connected with the study will set the stimulation characteristics as indicated by the information in a sealed envelope opened upon the participants’ visits (real or sham). The mode of stimulation will not be revealed to the participants or investigators.

### 2.4. Sample Size Calculation

The sample size was calculated using G*Power software according to the study of Charest et al. (2021) [23]. The study found d = 0.7012 for the Cohen’s effect size of tDCS on PSQI as the screening outcome of this study. Based on a 0.7012 effect size, bidirectional alpha of 0.05, and 80% test power, a minimum of 70 participants are required for this study. The sample will be increased by 20% to compensate for possible dropouts, and an overall sample of 84 participants will be included in this study.

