### 2.7. Primary Outcome Measures

#### 2.7.1. A-Sleep Monitoring

ActiGraph via synchronized wGT3X-BT software [25] will be used to objectively assess the physical activity parameters and sleep parameters. Actigraph is a valid and reliable tool for assessing sleep in healthy individuals [26]. The Actigraph sleep parameters are the following:i.Time in bed: the time between the ‘Lights Out’ and ‘Got Up’ times;ii.Actual sleep time: the total time spent sleeping according to the epoch-by-epoch wake or sleep categorization, excluding sleep latency and waking after sleep onset;iii.Wake after sleep onset: the amount of time a person spends awake, starting from when he or she first falls asleep to becoming fully awake and not attempting to go back to sleep;iv.Sleep efficiency: the ratio between the actual sleep time and time in bed.

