### 2.8. Secondary Outcome Measures

#### 2.8.1. A-PSQI

PSQI is a self-reported questionnaire with 19 questions that measure various aspects of sleep quality [29]. The response to the questionnaire is rated on a scale from 0 to 3, with 0 indicating no sleep difficulty and 3 indicating severe sleep difficulties. The PSQI global score ranges from 0 to 21, with a higher score indicating poor sleep quality. Individuals with a PSQI global score of >5 can be classified as having poor sleep quality. The PSQI has good psychometric properties in sport populations [30].

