In this protocol, tDCS parameters of a 1.5-mA intensity in 1 cm^2^ (0.057 mA/cm^2^ in density) for 20 min/session 6 times for 2 weeks will be used. The rationale for using 1.5 mA is to generate slow oscillation in the DLPFCs. The tDCS intensity ranges between 1 and 2 mA in sleep trials [16]. A previous study found that 1.5 mA is more effective than 1 mA in people with poor sleep quality [39]. The current parameters are considered safe based on data of more than 33,200 sessions and 1000 participants [40]. The study concluded that the tDCS protocols at ≤4 mA for ≤40 min had not produced any reports of a serious adverse effect or permanent injury [40].

The current study’s outcome measures include subjective and objective sleep measurements, psychological outcomes, and quality of life, which were not previously examined in athletic participants. A previous study [26] found low correlation between the subjective and objective sleep measures and recommended using subjective and actigraphy sleep measures to comprehensively assess sleep. Therefore, exploring the therapeutic effects of the bilateral anodal tDCS on different sleep parameters, quality of life, and psychological status in the athletic participants with sleep disorders may provide a promising noninvasive tool for athletic sleep disorder management.

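### The 80% power and the sample size of 70 (84 with dropout) are derived only for PSQI, a secondary outcome and entry criterion; no power is established for any primary outcome

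*Protocol article*

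**What the plan says.** Section 2.4 takes its only effect size from an earlier tDCS trial in athletes: "The study found d = 0.7012 for the Cohen’s effect size of tDCS on PSQI as the screening outcome of this study". It continues: "Based on a 0.7012 effect size, bidirectional alpha of 0.05, and 80% test power, a minimum of 70 participants are required for this study". It then adds the dropout allowance: "The sample will be increased by 20% to compensate for possible dropouts, and an overall sample of 84 participants will be included in this study".

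Elsewhere the article gives PSQI two roles, neither of them primary:

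- Section 2.1 requires a global PSQI score above 5 for entry.
- Section 2.8.1 lists PSQI first among the secondary outcomes ("PSQI is a self-reported questionnaire with 19 questions that measure various aspects of sleep quality").

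The primary outcomes are in Section 2.7:

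- Actigraphy, which "will be used to objectively assess the physical activity parameters and sleep parameters", with four sleep parameters: time in bed, actual sleep time, wake after sleep onset and sleep efficiency.
- The Insomnia Severity Index (ISI).
- The Epworth Sleepiness Scale (ESS).

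The Introduction says that the trial will assess subjective and objective sleep parameters "using a statistically powerful sample size". The Discussion justifies measuring both kinds by citing a study that "found low correlation between the subjective and objective sleep measures".

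**The concern.** A power statement belongs to one outcome, one effect size and one test. Here the outcome is PSQI, while the conclusion will rest on actigraphy, ISI and ESS. Nothing in the article argues that the PSQI effect of 0.7012 SD applies to them.

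Two misreadings could follow. A null result on a primary outcome could be taken as evidence from a trial with 80% power, although power for that outcome was never worked out. A positive PSQI result could be presented as the powered finding despite its secondary status.

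This is not a detail left to an analysis plan. Section 2.4 gives its source, effect size, alpha, sidedness, power, sample size and dropout allowance, and it names its outcome. A later document cannot change which outcome the 70 was derived from.

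**Working it through.** **Inputs.** From Section 2.4: d = 0.7012 on PSQI, two-sided alpha 0.05, power 80%, 70 in total, plus 20% for dropout. From Section 2.3: 1:1 allocation. For the primary outcomes the article gives no effect size, SD or baseline-to-follow-up correlation, so every such value below is an assumption.

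**Step 1. Reproduce the plan's figure for PSQI.** Let n be the number per arm.

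- Normal approximation: n = 2(1.960 + 0.842)²/d² = 2 × 7.85/0.4917 ≈ 31.9, so 32 per arm and 64 in total.
- Two-sample t test: power comes from the noncentral t with 2n − 2 degrees of freedom and noncentrality d√(n/2). At n = 33 power is 80.1%, so 66 in total. At n = 35 the noncentrality is 0.7012 × √17.5 ≈ 2.93 and power is 82.4%.
- Mann-Whitney test with normal data (efficiency 3/π): 33/(3/π) = 34.6, so 35 per arm and 70 in total, with power 80.6%.
- Dropout: 70 × 1.20 = 84.

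The stated 70 and 84 are reproduced with the Mann-Whitney option; the article does not say which test was used. The arithmetic for PSQI is not in question.

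**Step 2. Detectable effect for any other outcome at one time point.** With 35 completers per arm, two-sided 0.05 and 80% power:

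- t test: 0.68 SD (0.62 SD if all 42 per arm complete).
- Mann-Whitney: 0.68/√(3/π) = 0.68/0.977 ≈ 0.70 SD.

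**Step 3. Detectable effect for change from baseline.** Section 2.12 plans a group × time repeated-measures ANOVA over baseline, post-intervention and 1 month. For the baseline-to-post contrast within it, the SD of change is SD × √(2(1 − r)), where r is the correlation between the two measurements. The detectable effect in SD units of the outcome is therefore 0.679 × √(2(1 − r)).

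| Assumed r | √(2(1 − r)) | Detectable effect (SD) | Power if the true effect is 0.5 SD |
|---|---|---|---|
| 0.3 | 1.183 | 0.80 | 41% |
| 0.5 | 1.000 | 0.68 | 54% |
| 0.7 | 0.775 | 0.53 | 76% |
| 0.8 | 0.632 | 0.43 | 90% |

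So 0.68 SD is not a general figure. For change it holds only at r = 0.5.

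**Step 4. How much the missing effect size matters.** One time point, t test, 35 per arm:

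| Assumed true effect (SD) | Power | Total completers for 80% power |
|---|---|---|
| 0.6 | 70% | 90 |
| 0.5 | 54% | 128 |
| 0.4 | 38% | 200 |
| 0.3 | 24% | 352 |

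These rows show sensitivity to an unstated input. They are not estimates of the trial's power.

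**The case against.** Several points on the other side have force.

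- *Section 2.4 openly names PSQI.* A careful reader can see what the 80% refers to, and the Introduction's phrase follows a remark on the small sample of the earlier trial. That softens the charge, but the phrase is attached to the aim of assessing subjective and objective sleep parameters, so it still reads as a claim about the trial's main question.
- *ISI and ESS are self-reported, like PSQI.* The low correlation cited in the Discussion concerns subjective against objective measures and says nothing about these two. This stands. For them, the gap is simply that no argument or figure is offered.
- *Low correlation does not rule out similar standardized effects.* This also stands. A reader might infer from the Discussion that the PSQI effect cannot hold for actigraphy. The text supports only that the transfer is not established.
- *The repeated-measures analysis may be more efficient than a t test.* It may, if the correlation exceeds 0.5. At 0.3 the change contrast does worse. The article states no correlation, so the gain cannot be claimed.

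The stronger reading, that the trial is underpowered for its primary outcomes, is tempting but unsupported. The low power figures above rest on assumed effects. A primary outcome with a true effect near 0.70 SD, or a smaller effect with a high correlation, would have about 80% power or more.

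**Conclusion.** The point holds as a mismatch between the outcome used for sizing and the primary outcomes. The 80% power and the 70 (84) participants are derived for PSQI alone. Power for actigraphy, ISI and ESS is not established, so "using a statistically powerful sample size" is unsupported for the primary question.

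The size can be given only conditionally. With 35 completers per arm and each test at two-sided 0.05, the effect detectable with 80% power is about 0.68 SD (t test) or 0.70 SD (Mann-Whitney) at one time point. For baseline-to-post change it is 0.80 to 0.43 SD across assumed correlations of 0.3 to 0.8. These figures assume roughly normal data and equal variances, and they describe a two-time-point contrast rather than the full three-time-point interaction test. They use 0.05 because Section 2.12 plans no other level.

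**What to change.** Keep the current primary outcomes and the planned 84 participants, and make these changes before unblinding:

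1. In Section 2.4, state that the 80% power refers to PSQI, a secondary outcome, and name the test behind the 70.
2. In the same section, give the detectable effect for each primary outcome with its assumptions. Possible wording: With 35 completers per arm, two-sided alpha 0.05 and 80% power, the detectable difference in a primary outcome is about 0.68 SD for a t test at one time point (0.70 SD for Mann-Whitney); for change from baseline to post-intervention it is about 0.80, 0.68, 0.53 and 0.43 SD if the correlation is 0.3, 0.5, 0.7 and 0.8. Convert to minutes, percentage points or scale points wherever an SD can be justified.
3. In the Introduction, remove or qualify the claim of a powerful sample.

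If a multiplicity rule is later adopted for the primaries, recalculate these figures at that level.

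Making PSQI the primary outcome instead is not recommended. Recruitment began in May 2022 and the trial is registered, so this would replace every primary outcome mid-trial. It would also leave a self-report measure as the sole primary, when the Introduction itself names reliance on self-report as a limitation of the field.

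The cost is a few sentences. No participants, allocation or analysis change. The downside is that the stated power becomes less favourable for the primary outcomes.

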### 2.5. Procedures

The research procedure will be explained to eligible athletes if they agree to participate. Informed consent will be obtained from each participant. Figure 1 demonstrates the CONSORT flow diagram for this study. Baseline assessments (T0) will be conducted for demographic, health, and sport-related information, clinical characteristics, and primary and secondary outcome measures at baseline. Post intervention assessments (T1) for comparing the immediate efficacy between the two groups of primary and secondary outcome measures will be performed directly after completion of the intervention protocol. Follow-up assessments (T2) will be conducted 1 month after the end of the intervention.

### 2.6. Assessments and Outcome Measures

Demographics include the date of birth, educational level, marital status, weight, and height. Health-related questions concern the diagnosis of any other disorders and current medications used. Sport-related information that will be gathered includes the type and level of sport, number of years in practice, number of times they practice per week, and for how long.

All assessment instruments will be used in their validated Arabic versions. The primary and secondary outcome measures include both subjective and objective sleep outcomes.

### 2.7. Primary Outcome Measures

#### 2.7.1. A-Sleep Monitoring

ActiGraph via synchronized wGT3X-BT software [25] will be used to objectively assess the physical activity parameters and sleep parameters. Actigraph is a valid and reliable tool for assessing sleep in healthy individuals [26]. The Actigraph sleep parameters are the following:i.Time in bed: the time between the ‘Lights Out’ and ‘Got Up’ times;ii.Actual sleep time: the total time spent sleeping according to the epoch-by-epoch wake or sleep categorization, excluding sleep latency and waking after sleep onset;iii.Wake after sleep onset: the amount of time a person spends awake, starting from when he or she first falls asleep to becoming fully awake and not attempting to go back to sleep;iv.Sleep efficiency: the ratio between the actual sleep time and time in bed.

#### 2.7.2. B-Insomnia Severity Index (ISI)

The ISI will be used to quantify the severity of sleep impairments during the nights of the previous month [27]. ISI is a self-reported questionnaire that includes seven questions. The total score of the ISI ranges between 0 and 28, with a higher score indicating more severe insomnia.

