### 2.9. Intervention

Depending on the randomization allocation, participants will receive either a real tDCS or sham tDCS protocol for three sessions per week for 2 weeks, with a total of six sessions. 

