### 2.12. Statistical Analysis

The participants’ characteristics and outcome measures at baseline will be compared between the two groups using the Kruskal–Wallis test. Data will be screened for missing data, normality, and outliers. For variables that are not normally distributed, non-parametric tests will be used. The normally distributed data will be analyzed by repeated measures analysis of variance (ANOVA) to evaluate the therapeutic effect and changes between the two groups and within groups (group: sham vs. real tDCS) × (time: pre- vs. post-intervention vs. 1-month follow-up). Post hoc analysis will be applied to determine the exact groups with significant changes if significant findings appear. For the variables not normally distributed, we will use Friedmann’s test. The correlation between the changes in the Actigraph results with the athletes’ characteristics, DAAS-21, SF-12 pain, general health, role (emotional), and mental health domains at baseline will be analyzed by repeated measures linear regressions to understand the mechanism of improvement. The data will be analyzed using SPSS software, and a conservative *p*-value of 0.05 will be considered.

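### The ISI, a primary outcome, looks back one month, but T1 closes a 2-week course, so about half of the T1 window predates treatment and the T1 contrast is diluted

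*Protocol article*

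**What the plan says.** The ISI is the second of three measures under the heading "2.7. Primary Outcome Measures", between actigraphy and the Epworth Sleepiness Scale (ESS). Section 2.7.2 gives its recall period: the ISI is to "quantify the severity of sleep impairments during the nights of the previous month".

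Section 2.9 sets the course at "three sessions per week for 2 weeks, with a total of six sessions". Under section 2.5, the T1 assessment "will be performed directly after completion of the intervention protocol", and its purpose is "comparing the immediate efficacy between the two groups of primary and secondary outcome measures". The same section adds: "Follow-up assessments (T2) will be conducted 1 month after the end of the intervention".

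Section 2.12 analyses normally distributed outcomes by repeated measures ANOVA of group by time, with the time factor defined as "time: pre- vs. post-intervention vs. 1-month follow-up". Nothing in the article shortens the ISI recall period at T1 or names one visit as the key one for the ISI.

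**The concern.** The recall period, the length of the course and the purpose of T1 do not fit together. A one-month window that closes at the end of a 2-week course takes in roughly two weeks before the first session. On those nights randomised arms cannot differ because of treatment. A participant who answers as instructed reports a mixture of untreated and treated nights, and the between-arm difference at T1 shrinks.

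Two readings are at stake. A small T1 difference on a primary outcome might be taken as absence of immediate efficacy. And because the T2 window lies wholly after treatment, a constant true effect could appear to grow from T1 to T2, which post hoc comparisons might present as a delayed benefit.

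**Working it through.** **Inputs from the protocol article.** ISI recall of one month (2.7.2). Course of 2 weeks (2.9). T1 directly after the course and T2 one month later (2.5). d = 0.7012, two-sided alpha 0.05, 80% power, 70 participants raised to 84 (2.4). Allocation 1:1 (2.3). The value of d is for the PSQI; no ISI effect size is given.

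**The plan's own figure.** A two-sample t-test with d = 0.7012 needs 33 per arm (66 in all, power 80.1%). The Wilcoxon-Mann-Whitney version, with relative efficiency 3/π, needs 35 per arm, which is the stated 70. Then 70 × 1.20 = 84. I use 35 per arm below.

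**Share of the T1 window before treatment** = 1 − course days / recall days:
- 28-day month: 1 − 14/28 = 50%
- 30-day month: 1 − 14/30 = 53%
- 31-day month: 1 − 14/31 = 55%

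If the six sessions span only 12 days, the share is 57% (1 − 12/28) to 61% (1 − 12/31). At T0 the share is 100%. At T2 it is 0%, because the window reaches back only to the end of the course.

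**Effect retained at T1.** Assume that recall averages nights equally, that the effect is full from the first session, and that the SD is unchanged. The retained fraction is then 14/31 to 14/28, or 45% to 50%. With 0.7012 as a stand-in for the true ISI effect, d at T1 is 0.7012 × 0.452 = 0.317 to 0.7012 × 0.5 = 0.351.

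**Power of a T1 comparison on its own** (two-sided t-test, noncentrality d × √(n/2), 35 per arm):

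| Effect retained at T1 | d | Power |
|---|---|---|
| 100% | 0.701 | 82% |
| 75% (recent nights weigh more) | 0.526 | 58% |
| 50% | 0.351 | 30% |
| 45% | 0.317 | 26% |

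With all 84 participants retained (42 per arm), the full effect gives 89%, and 45-50% of it gives 30-36%.

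**Power of the planned group by time test.** Assume equal variances and a common within-person correlation ρ. The noncentrality is λ = (n/2) × SS / (1 − ρ), where SS is the sum of squared deviations of the three between-arm differences from their mean, with 2 and 136 degrees of freedom. Take the effect as sustained to T2, n = 35 and ρ = 0.5:
- Undiluted, differences (0, d, d): SS = (2/3)d² = 0.328, λ = 11.47, power 86%.
- T1 halved, differences (0, d/2, d): SS = (1/2)d² = 0.246, λ = 8.60, power 74%.

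At ρ = 0.3 the same pair is 72% and 59%; at ρ = 0.7 it is 98% and 93%. If instead the effect has gone by T2, the differences change from (0, d, 0) to (0, d/2, 0), SS falls from 0.328 to 0.082, and power at ρ = 0.5 falls from 86% to 30%.

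**The case against.** The strongest objection is that the main test is not a T1 comparison. Section 2.12 plans a group by time analysis that includes T2, where the ISI window is clean. A reader might infer from the T1 figures that power for the ISI collapses. The documents do not support that: with an effect sustained to T2, the planned test loses about 12 percentage points at ρ = 0.5. The loss is much larger if the effect fades, but the article does not say whether it expects fading.

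The effect size is also borrowed. It is a PSQI result from an earlier study whose visit timing and recall are not shown; if it was already diluted, halving it counts the dilution twice. Respondents may weight recent nights more heavily, which makes the dilution smaller without reversing it. The bias is conservative, so it creates no false claim of benefit at T1. All of this stands, and it limits the power figures to illustration.

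Three further inferences go too far:
- That any T1-to-T2 growth would be an artefact. A real delayed effect would look the same, so only part of the growth could be attributed to the window.
- That the T0 and T1 windows overlap by two weeks. This needs T0 to fall immediately before the first session, and section 2.5 gives no interval.
- That the other questionnaires share the problem. Sections 2.7.3 to 2.8.3 state no recall period for them.

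**Conclusion.** The mismatch is real and comes from the protocol's own statements. About 50-55% of the ISI window at T1 precedes the first session with a 14-day course. The direction follows from the design: to the extent that participants use the stated recall period, any true T1 difference is shrunk towards zero. High confidence belongs to the overlap and the direction only.

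The size is conditional. Retaining 45-50% of the effect requires equal weighting of nights and an immediate effect; an effect that builds during the course would leave less, and recall that favours recent nights would leave more. The power figures also need the PSQI effect size, an unchanged SD and, for the group by time test, an assumed correlation.

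The problem is confined to one of three primary measures at one visit, and to the T1-to-T2 trajectory of that measure. It should be corrected, but it does not undermine ISI at T2, or the actigraphy and ESS results, for which the article states no one-month recall.

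**What to change.** **Preferred, before unblinding.** Prespecify T2 as the key ISI time point. Label T1 ISI as supportive and diluted by its recall window. State that growth in the ISI effect from T1 to T2 will not be interpreted as a delayed benefit.

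This needs no new data and fits what has been collected since recruitment began in May 2022. It does change the question, however: T2 measures persistence, so immediate efficacy would rest on actigraphy and the ESS. Because the trial is registered and recruiting, the change must be documented as an amendment.

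**Alternative.** Use an ISI recall period no longer than the 2-week course at T0, T1 and T2. This keeps T1 as a measure of immediate efficacy. The costs are inconsistency with participants already assessed and a possible departure from the validated Arabic version to which section 2.6 commits. It should be adopted only if that version allows the shorter period.
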